### Data analysis

Analyses will be conducted with the most recent version of the software “IBM SPSS Statistics,” currently version 27.0. Adolescents are analyzed as randomized if they participated in at least one DELTA session (DELTA condition only). To test all non-descriptive hypotheses (see below, hypotheses 2–4), a repeated measures MANOVA will be conducted using time as factor (“within factor”) given the explanatory nature of the trial and the non-importance of between-group effects. A significant reduction over time (BL vs. FU) in all *N* = 40 participants across all metric outcomes (MaCS score, FTND score, DUDIT score, AUDIT score, and cigarettes per day during the past month according to substance use interview) indicates a relevant intervention effect. This multivariate approach will limit the chance for false-positive results as otherwise possible due to multiple testing. Effect sizes will be classified into small effects (ƞ^2^ ≥ 0.01), medium effects (ƞ^2^ ≥ 0.06), and large effects (ƞ^2^ ≥ 0.14). In case of severe non-normality of outcome variables, we will have to apply non-parametric tests instead of the repeated measures MANOVA.

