#### Hypotheses

Aim (A) is reached when for each need, identified through qualitative analyses of interviews, one or more adjustments to the content or procedure of DELTA-JU is documented. No quantitative hypothesis is applicable. Aims (B) and (C) are achieved through testing the following hypotheses in adolescents who are abstinent for alcohol and drugs except nicotine/tobacco:
Adolescents: relevant increase in SUD-related subjective utility through FU (descriptive: a medium rating of 2.0 or higher in the respective GEJ items across participants);Adolescents: significant reduction of substance-related craving as a measure of relapse risk (*p* < 0.05, MaCS score) through FU;Adolescents: significant reduction of SUD severity (*p* < 0.05, scores of FTND, AUDIT, and DUDIT) through FU;Adolescents: significant reduction of self-reported past-month tobacco use through FU (*p* < 0.05, substance use interview);Personnel: relevant increase in SUD-related subjective utility through FU (descriptive: a medium rating of 2.0 or higher in the respective GEB items across participating personnel); andPersonnel: high satisfaction ratings concerning the workshop organization (descriptive: a medium rating of 4.0 or higher in the respective GEB items across participating personnel).

Additionally, secondary outcomes in adolescents (BDI-II, PQ-16, UCLA-PTSD, PSS-10, and SWLS) and personnel (ERI-S-10) will be tested exploratorily for changes through FU as previously done in the DELTA evaluation (15). All reductions through FU in adolescents are expected to be descriptively larger than reductions over the natural course, i.e., from PRE to BL in the WL group.

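### One non-directional MANOVA cannot decide three separate "reduction" hypotheses, and it limits false positives only when no outcome changes

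*Protocol article*

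**What the plan says.** Under Data analysis, the protocol article states: "To test all non-descriptive hypotheses (see below, hypotheses 2–4), a repeated measures MANOVA will be conducted using time as factor". The success criterion is a significant drop from baseline to follow-up "across all metric outcomes (MaCS score, FTND score, DUDIT score, AUDIT score, and cigarettes per day during the past month" (the last taken from the substance use interview), which "indicates a relevant intervention effect". The article then gives its multiplicity rationale: "This multivariate approach will limit the chance for false-positive results as otherwise possible due to multiple testing". Eta-squared cut-offs of 0.01, 0.06 and 0.14 follow ("Effect sizes will be classified into small effects" and so on). If the outcomes are severely non-normal, "we will have to apply non-parametric tests instead of the repeated measures MANOVA".

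Under Hypotheses, the same claims appear as three directional statements, each with its own threshold. Hypothesis 2 is a "significant reduction of substance-related craving as a measure of relapse risk (*p* < 0.05, MaCS score) through FU". Hypothesis 3 is a reduction in severity at p < 0.05 on three instruments ("scores of FTND, AUDIT, and DUDIT) through FU"). Hypothesis 4 is a reduction in past-month tobacco use at p < 0.05.

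Under Estimation of sample size, N = 40 analysed adolescents is derived from α = 0.05, power 0.95, f = 0.40 and a repeated measures correlation of 0.1.

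**The concern.** The test named in one section does not answer the questions asked in the other. A significant joint time effect says that some combination of the five scores moved, up or down. It does not say which score moved, or that any fell. To confirm hypothesis 2 and not hypothesis 4, say, the analyst needs single-outcome results, and the article gives no rule for reading them.

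The multiplicity statement matters for the same reason. A joint test used as a gate controls the error only while every null hypothesis is true. Once one score really moves, the gate opens almost every time and the other scores are unprotected. A mixed picture is plausible here. The introduction reports that nicotine use did not fall in the earlier evaluation. AUDIT and DUDIT look back 12 months, while residents are generally abstinent from the start of their stay. Some scores may move while others do not.

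At stake is whether a positive conclusion on craving, severity or tobacco use can be trusted, and whether the sample size supports the success rule in use.

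**Working it through.** **Inputs from the protocol article.** Five outcomes, two time points, N = 40, α = 0.05, f = 0.40, r = 0.1, power 0.95. **Assumption:** the correlation among the five change scores is not given, so 0 to 0.5 is shown.

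**1. Reproduce the planned sample size.** For a within-subject F test with m = 2 time points, λ = f²·N·m/(1 − r).
- At N = 40: λ = 0.16 × 40 × 2 / 0.9 = 14.2 on 1 and 39 degrees of freedom, giving power 0.957.
- The smallest N reaching 0.95 is 39, so the stated 40 is confirmed.
- A one-sided 0.05 test would need only 32, so the figure is two-sided and for one outcome.
- The equivalent standardised mean change is dz = √(0.16 × 2 / 0.9) = 0.596.

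**2. What the MANOVA tests.** With two time points it is a one-sample Hotelling T² test on five change scores, which is non-directional. I simulated trials of N = 40 in which one outcome truly *rises* (dz 0.596) and the other four do not change:
- the MANOVA is significant in 77–95% of trials;
- in 68–88% of all trials it is significant with no significant reduction on any outcome.

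**3. Chance of at least one false finding,** simulated for correlations 0 to 0.5, each follow-up test at two-sided 0.05:

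| Situation | Either direction | Reductions only |
|---|---|---|
| Nothing changes; MANOVA, then unadjusted tests | 3.7–4.6% | 1.9–2.7% |
| One true reduction (dz 0.596), four nulls; MANOVA, then unadjusted tests | 15–17% | 8–9% |
| Nothing changes; fallback as five separate unadjusted tests | 18–23% | 9–12% |

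The fallback's upper ends follow from independence: 1 − 0.95⁵ = 0.226 and 1 − 0.975⁵ = 0.119. In the second row the gate removes little. Without it, the either-direction figure is 16–18%. Holm across the five scores keeps the chance of any false finding below 5% in every scenario run.

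**4. The all-outcomes reading.** If all five must be significant, no adjustment is needed. With every outcome at the planned effect, power under independence is 0.957⁵ = 0.80, rising to about 0.85 at correlation 0.5.

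**5. Effect-size labels.** With no true change, the multivariate eta-squared for five outcomes at N = 40 follows Beta(5/2, 35/2), with mean 2.5/20 = 0.125. A single-outcome eta-squared follows Beta(1/2, 39/2), with mean 0.5/20 = 0.025. The cut-offs therefore mean different things on the two scales.

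**The case against.** The strongest reply is that only a condensed article is shown. Follow-up tests, the named non-parametric test and any adjustment may sit in an analysis plan. The article describes a phase 2 pragmatic trial with a simplified analysis, claims only to *limit* false positives, and can be read as requiring all five reductions.

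Much of this stands, and it rules out several stronger readings:

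- *Five claims, each tested at p < 0.05.* The article has three such hypotheses covering five scores, and hypothesis 3 does not say whether all or any of its scores must fall.
- *The protection does not exist.* It does exist when nothing changes. It is partial.
- *The false-claim risk is simply 18.5% (1 − 0.95⁴) or 22.6%.* Those figures assume independence and count false increases as well. The hypotheses concern reductions, for which the risk is about half.
- *The fallback is certainly uncorrected.* That would be inferred from silence, so the fallback figures are conditional on five separate unadjusted tests.
- *Null results will be labelled medium or large.* The article does not say that the cut-offs apply to the multivariate statistic. Applied per outcome, chance alone reaches 0.14 in only 1.6% of cases.

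The reply does not remove the mismatch. The article itself names the test, the thresholds, the fallback and the multiplicity rationale, and they do not fit together. The all-outcomes reading does not rescue the plan either: the MANOVA does not test it, and the sample size was not computed for it.

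**Conclusion.** The point holds as a mismatch between the named test and the stated hypotheses. One joint, non-directional p-value cannot decide hypotheses 2–4, and the Data analysis and Hypotheses sections do not fix a single decision rule.

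The consequence depends on the rule eventually used. Hypothesis by hypothesis without adjustment, the false-positive claim fails once any outcome moves, or once the MANOVA is replaced by separate tests. With an all-five rule, the error rate is sound and the stated power is too high. The sizes rest on normally distributed change scores, equal correlations of 0 to 0.5 and the plan's own effect size; the conclusion is the same across that range. N = 40 is correct for a single outcome and is not in dispute.

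**What to change.** Choose one decision rule and use the same rule in both sections and in the fallback.

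- **Preferred:** test the five scores one by one, require the change to be a reduction, and apply Holm across the five. State whether hypothesis 3 needs all or any of its three scores. Apply the same rule to the non-parametric tests. Keep the MANOVA as descriptive and remove it as the multiplicity safeguard.
- **Alternative:** state that all five reductions must be significant, make no adjustment, and restate the power as about 0.80–0.85.

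In either case, apply the 0.01/0.06/0.14 labels only to single-outcome eta-squared.

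The cost is wording, plus some power under Holm. The smallest p-value is compared with 0.05/5 = 0.01, and at that level per-outcome power at N = 40 is about 0.85 instead of 0.957. Restoring 0.95 at 0.01 would take 54 analysed adolescents, or 54/0.8 = 67.5, so 68 enrolled at the planned 20% dropout. If recruiting that many is not feasible, report the lower power.

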#### Hypotheses

Aim (A) is reached when for each need, identified through qualitative analyses of interviews, one or more adjustments to the content or procedure of DELTA-JU is documented. No quantitative hypothesis is applicable. Aims (B) and (C) are achieved through testing the following hypotheses in adolescents who are abstinent for alcohol and drugs except nicotine/tobacco:
Adolescents: relevant increase in SUD-related subjective utility through FU (descriptive: a medium rating of 2.0 or higher in the respective GEJ items across participants);Adolescents: significant reduction of substance-related craving as a measure of relapse risk (*p* < 0.05, MaCS score) through FU;Adolescents: significant reduction of SUD severity (*p* < 0.05, scores of FTND, AUDIT, and DUDIT) through FU;Adolescents: significant reduction of self-reported past-month tobacco use through FU (*p* < 0.05, substance use interview);Personnel: relevant increase in SUD-related subjective utility through FU (descriptive: a medium rating of 2.0 or higher in the respective GEB items across participating personnel); andPersonnel: high satisfaction ratings concerning the workshop organization (descriptive: a medium rating of 4.0 or higher in the respective GEB items across participating personnel).

Additionally, secondary outcomes in adolescents (BDI-II, PQ-16, UCLA-PTSD, PSS-10, and SWLS) and personnel (ERI-S-10) will be tested exploratorily for changes through FU as previously done in the DELTA evaluation (15). All reductions through FU in adolescents are expected to be descriptively larger than reductions over the natural course, i.e., from PRE to BL in the WL group.

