#### Setting and participants

Youth welfare institutions will be approached if they are in the study region (district of Saxony and, if feasible, surrounding areas in Brandenburg and Thuringia). Generally, those institutions specialized in SUD care are placed outside of metropolitan areas (32) in order to reduce risk factors for relapse (such as contact to drug dealers) (33). Adolescents and their legal guardians will be approached by personnel of participating institutions. If interested, study personnel will hand out information material and will answer all questions in person, via telephone or via e-mail. Consent will be given after additional verbal information to adolescents. Inclusion criteria for adolescents are: (1) aged 12.00–17.99 years, (2) SUD diagnosis, or (3) chronic substance use during the past. The only exclusion criterion is low cognitive functioning (intelligence quotient <70). For BL-FU analyses, we will not analyze participants who did not attend any of the 16 sessions for whatever reason or if study participation was discontinued due to an adverse event. Participants choosing to discontinue are immediately asked whether they want to provide data on primary outcomes anyhow. Personnel of youth welfare institutions is included if they work with at least 20 h/week in a cooperating institution. The anticipated flow of adolescent participants is shown in Figure 2. At the time of writing this protocol, study registration is completed (01. Feb 2022) and the first adolescent participants are being recruited, randomized, and enrolled (starting 02. Feb 2022).

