## Discussion

The DELTA-JU study will create a setting-specific manual for highly vulnerable adolescents who suffer from one or more SUDs, and, in many cases, from co-occurring mental disorders. We believe that DELTA-JU will be (a) properly adjusted to setting-specific needs of youth welfare institutions offering housing for adolescents with SUD, (b) accepted both by adolescents and the institutions’ personnel, and (c) effective in remaining abstinent from substances, reducing tobacco smoking, and reducing SUD problems. Providing feasible and effective treatments that are accepted by their respective target population is one primary goal set both for mental health research and practice in Europe (65).

As in all interventions, an age-specific approach is warranted when approaching children and adolescents. DELTA and DELTA-JU indeed provide an age-adequate intervention that includes material, methods, and content created for adolescents’ needs specifically while avoiding topics and approaches better suited for adults or older adults, e.g. (66). Furthermore, DELTA and DELTA-JU integrate modules on prevalent and outcome-relevant problems besides SUD, i.e., for depressiveness, for emotion regulation, and coping with stress and boredom. Addressing such co-occurring psychopathologies is in line with current recommendations for state-of-the art psychotherapeutic treatments (67). In the future, psychotherapeutic interventions such as DELTA-JU may be accompanied by including virtual reality elements or mobile phone-based elements.

Giving that effects can be independently replicated, it can be disseminated within other institutions of youth welfare. This will help institutions to professionalize their service for adolescents with SUD and it provides another currently lacking tool (68) for the outpatient treatment of SUDs before and after inpatient detoxification treatment (69). At the same time, we believe that besides treatment for diagnosed SUDs, efforts in prevention and early intervention are necessary nonetheless (70).

From a long-term perspective, programs such as DELTA-JU may help to alleviate the immense societal costs relating to consequences of alcohol use (27pprox. 32.5 billion EUR per year in Germany) (71), tobacco use (97.2 billion EUR) (72), cannabis use (0.9 billion EUR) (73), and the use of further substances for which no estimations are available.

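### The Hypotheses section limits testing to abstinent adolescents, with no time point, while the Data analysis section tests the same hypotheses in all 40 participants

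*Protocol article*

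**What the plan says.** **Hypotheses section.** Aims B and C are to be achieved by "testing the following hypotheses in adolescents who are abstinent for alcohol and drugs except nicotine/tobacco". Six hypotheses follow. Hypotheses 2–4 are the inferential ones: craving (MaCS), SUD severity (FTND, AUDIT, DUDIT) and past-month tobacco use. No time point or method of ascertainment is attached to abstinence.

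**Data analysis section.** The same hypotheses 2–4 go into one repeated-measures MANOVA with time as the factor. The criterion is "A significant reduction over time (BL vs. FU) in all" N = 40 "participants across all metric outcomes". The stated condition for entering the analysis is attendance: "Adolescents are analyzed as randomized if they participated in at least one DELTA session (DELTA condition only").

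**Setting and participants section.** Entry does not depend on current abstinence: "Inclusion criteria for adolescents are: (1) aged 12.00–17.99 years, (2) SUD diagnosis, or (3) chronic substance use during the past". On the other side, "The only exclusion criterion is low cognitive functioning". Two removals from the baseline-to-follow-up (BL–FU) analysis are named: "we will not analyze participants who did not attend any of the 16 sessions for whatever reason", and discontinuation because of an adverse event. Relapse is not among them.

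**Estimation of sample size section.** Fifty adolescents are to be included so that 40 can be analysed. The only allowance is 20% dropout.

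**The concern.** The two rules give the same dataset only if every participant is abstinent on whatever definition is meant. The protocol does not assume that. Its section on setting specifics in content calls residents abstinent at the start of their stay in general, not without exception. The manual before revision includes sporadic urine tests and several relapse sessions.

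Two things are at stake.

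- **Selection on an outcome.** If abstinence is judged at follow-up or throughout, those who relapse during treatment leave the test. They are the participants most likely to get worse on craving, AUDIT and DUDIT. The primary test is a one-sample change over time, so no between-arm contrast would expose the selection.
- **Analysed number.** If abstinence is judged at baseline, that bias does not arise, but any non-abstinent entrants removed come out of the 40 on which power rests.

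Blinding of the analysis is stated to be infeasible. With two written rules and no time point, the choice could be made after the data have been seen.

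**Working it through.** **1. The protocol's own figure.** Inputs from Estimation of sample size: α = 0.05, power 0.95, f = 0.40 for time, r = 0.1. There are m = 2 measurements (BL, FU). For a within-subject factor in the G*Power convention, one group:

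λ = f² × N × m / (1 − r), with a noncentral F on 1 and N − 1 degrees of freedom.

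- N = 39: λ = 0.16 × 39 × 2 / 0.9 = 13.87, power 0.952. This is the smallest N that reaches 0.95.
- N = 40: λ = 14.22, power 0.957.
- Dropout: 40 / (1 − 0.20) = 50.

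The stated 40 and 50 are reproduced. Nothing in them allows for removing non-abstinent participants.

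**2. Power if some of the 40 are removed.** The documents give no rate of non-abstinence, so the shares are assumptions. The last column keeps 40 abstinent participants in the analysis after 20% dropout: 40 / (1 − share) / 0.80, rounded up.

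| Assumed share removed | N analysed | λ | Power | Enrolment needed |
|---|---|---|---|---|
| 0% | 40 | 14.22 | 0.957 | 50 |
| 10% | 36 | 12.80 | 0.935 | 56 |
| 25% | 30 | 10.67 | 0.884 | 67 |
| 40% | 24 | 8.53 | 0.799 | 84 |

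This loss applies under any definition of abstinence that removes people.

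**3. Bias if abstinence is judged at follow-up or throughout.** This is an illustration with assumed values. There are 40 participants and no mean change overall. Relapsers (share p) worsen by 1 SD of change. The others improve by p / (1 − p), so that the two cancel: p × 1 − (1 − p) × p / (1 − p) = 0. Dropping relapsers leaves a mean change of −p / (1 − p). The rejection rates come from simulation, counting significant reductions with a two-sided 5% paired t-test. In all participants that rate is about 0.025, as it should be.

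| Assumed relapse p | Mean change, relapsers dropped (SD) | Chance of a significant reduction |
|---|---|---|
| 10% | −0.11 | about 0.10 |
| 20% | −0.25 | about 0.28 |
| 30% | −0.43 | about 0.58 |
| 40% | −0.67 | about 0.88 |

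The direction does not depend on the chosen values as long as relapsers do worse than the others; the size does. AUDIT and DUDIT cover 12 months, so their scores may register a recent relapse less sharply than this single generic outcome.

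**4. Bias if abstinence is judged at baseline.** Anyone who relapses between BL and FU stays in. The selection in step 3 does not occur, and only the loss in step 2 remains.

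**The case against.** The strongest reply is that the clause describes the setting and is not an analysis-set rule. Several features support this. Residents are said to be generally abstinent when their stay begins. The Adjustment stage section describes the institutions as serving abstinent adolescents. Smoking is the only use that house rules permit, which matches the exception for nicotine. The same lead-in also covers hypotheses 5 and 6, which concern personnel, so it is loosely drafted. The attendance rule, the named removals and the step from 50 to 40 all contain no relapse exclusion.

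This makes a descriptive or baseline reading plausible, and it rules out saying that the plan does remove relapsers. It does not settle which population is tested: the clause is still written as a condition on the tests, and no time point is given.

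Two stronger readings are tempting and are not supported.

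- **A reader might infer that relapse becomes invisible.** It does not. Use of other substances is recorded by interview at PRE, BL and FU and is to be explored, and AUDIT and DUDIT are in the primary MANOVA. The article also says openly that objective relapse measures were not funded.
- **A reader might infer that the trial's main claim goes untested.** The Discussion does express a belief that the programme will be "effective in remaining abstinent from substances, reducing tobacco smoking, and reducing SUD problems". Aim C, however, is reduced substance use including tobacco and reduced SUD problems. Remaining abstinent is not a formal aim.

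**Conclusion.** The contradiction stands on the text: one section restricts hypotheses 2–4 to abstinent adolescents, another tests them in all 40, and the eligibility, removal and sample size statements fit only the second. The time point of abstinence is undefined.

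The consequence is conditional. A definition at follow-up or throughout would bias the primary test towards benefit, by an amount that rests wholly on assumed relapse rates and effects. A baseline definition carries no such bias but costs power: 0.935 at N = 36 and 0.884 at N = 30, against 0.957 at 40. These figures use the protocol's f = 0.40 and r = 0.1 with assumed shares removed. If nobody is removed, nothing changes numerically. The correction is still worth making, because the restriction as written permits conditioning the primary test on a post-treatment outcome and removing it costs almost nothing.

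**What to change.** - **Hypotheses section:** delete the abstinence restriction. State that hypotheses 2–4 are tested in the population of the Data analysis section, and that participants who relapse are kept.
- **If an abstinent subset is wanted:** define it only by status at each arm's own BL and label it secondary. In Table 1, BL is week 0 for the immediate arm and week 17 for the waitlist arm. Week 0 should not serve as the common time point, because for the waitlist arm it is the PRE assessment.
- **Addition:** tabulate past-month alcohol and illicit drug use from the existing interview at PRE (waitlist arm), BL and FU.

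The cost is a change of wording and one table from data already collected. The drawback of the table is that it rests on self-report without objective confirmation.
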